## Abstract

**Background:**

Approximately 20% of patients experience chronic pain after total knee replacement. There is little evidence for effective interventions for the management of this pain, and current healthcare provision is patchy and inconsistent. Given the complexity of this condition, multimodal and individualised interventions matched to pain characteristics are needed. We have undertaken a comprehensive programme of work to develop a care pathway for patients with chronic pain after total knee replacement. This protocol describes the design of a randomised controlled trial to evaluate the clinical- and cost-effectiveness of a complex intervention care pathway compared with usual care.

**Methods:**

This is a pragmatic two-armed, open, multi-centred randomised controlled trial conducted within secondary care in the UK. Patients will be screened at 2 months after total knee replacement and 381 patients with chronic pain at 3 months postoperatively will be recruited. Recruitment processes will be optimised through qualitative research during a 6-month internal pilot phase. Patients are randomised using a 2:1 intervention:control allocation ratio. All participants receive usual care as provided by their hospital. The intervention comprises an assessment clinic appointment at 3 months postoperatively with an Extended Scope Practitioner and up to six telephone follow-up calls over 12 months. In the assessment clinic, a standardised protocol is followed to identify potential underlying causes for the chronic pain and enable appropriate onward referrals to existing services for targeted and individualised treatment. Outcomes are assessed by questionnaires at 6 and 12 months after randomisation. The co-primary outcomes are pain severity and pain interference assessed using the Brief Pain Inventory at 12 months after randomisation. Secondary outcomes relate to resource use, function, neuropathic pain, mental well-being, use of pain medications, satisfaction with pain relief, pain frequency, capability, health-related quality of life and bodily pain. After trial completion, up to 30 patients in the intervention group will be interviewed about their experiences of the care pathway.

**Discussion:**

If shown to be clinically and cost-effective, this care pathway intervention could improve the management of chronic pain after total knee replacement.

**Trial registration:**

ISRCTN registry (ISRCTN92545361), prospectively registered on 30 August 2016.

**Electronic supplementary material:**

The online version of this article (10.1186/s13063-018-2516-8) contains supplementary material, which is available to authorized users.

## Background

Treatment of osteoarthritis with total knee replacement aims to reduce pain, functional limitations and associated disability. Over 100,000 primary total knee replacements were performed in the United Kingdom (UK) in 2015 [1, 2]. Despite good outcomes for many, a systematic review found that approximately 20% of patients report chronic pain after total knee replacement [3]. Chronic post-surgical pain is defined as pain that occurs or increases in intensity at 3 months or longer after surgery [4]. Patients with bothersome pain at 3 months after surgery are often disappointed with their outcome [5, 6], feel abandoned by healthcare [7] and struggle to make sense of ongoing pain [8]. Chronic pain after knee replacement is an under-investigated area, but the wider literature shows the impact of chronic pain on all areas of life. Chronic pain is associated with poor general health, interference with daily activities, disability and depression [9–11]. Compared with the general population, patients with chronic musculoskeletal pain report lower satisfaction with life [12–14]. Older people with pain are likely to become socially isolated, which is a risk factor for other problems [15], limiting their capacity to bring about change or to seek help for their pain.

Healthcare provision for patients with chronic pain after total knee replacement has been shown to be patchy and inconsistent in the UK, with only some orthopaedic centres having standardised protocols to guide the assessment and management of patients with this condition [16]. A systematic review identified that only one trial has evaluated an intervention for the management of chronic pain after knee replacement – an injection with antinociceptive and anticholinergic activity [17]. There is also insufficient evidence about the effectiveness of interventions for the management of chronic pain after any surgery type [18]. Therefore, there is a need for robust evidence to guide the early screening, identification and management of patients with chronic pain after total knee replacement.

Treatment of chronic pain is challenging, and evaluation of treatments in combination or matched to patient characteristics is advocated [19], yet no such trials have been evaluated in the context of chronic post-surgical pain [18]. It has been argued that rather than new interventions for pain, improvements are required to access existing treatments with combination treatments matched to pain characteristics [19]. Chronic pain after total knee replacement may be caused by biological and mechanical factors. Biological causes include the sensitising impact of chronic pain from osteoarthritis [20–22], development of Complex Regional Pain Syndrome [23–25], persistent postoperative inflammation, infection and/or localised nerve injury [26]. Mechanical causes include altered gait, prosthesis loosening, and weakening effects on ligaments [27, 28]. Psychological factors may also influence postoperative outcomes [29].

To improve the management of chronic pain after total knee replacement, we have developed the STAR (Support and Treatment After joint Replacement) care pathway [30], which consists of early postoperative screening to identify patients with pain and an assessment clinic at 3 months postoperatively with an Extended Scope Practitioner and telephone follow-up, as required. The intervention aims to enable appropriate onwards referral to existing services to ensure that underlying reasons for chronic pain are considered early in the postoperative pathway and that treatment is targeted at these to improve pain management and to reduce the impact of pain. In line with UK Medical Research Council guidance on complex interventions, comprehensive development work has been undertaken to design and refine this intervention. The design of the intervention is underpinned by a systematic review [17], survey of current practice [16], focus groups with health professionals [31], expert deliberation and patient involvement activities [32]. Further development and refinement work included consensus work with health professionals to refine intervention content, testing intervention delivery and acceptability to patients, and evaluation of views about implementation of the intervention within the context of a randomised controlled trial [30]. The aim of this multi-centre randomised controlled trial is to evaluate the clinical and cost-effectiveness of the care pathway for patients with chronic pain after total knee replacement.

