#### Screening process to identify patients with chronic pain after knee replacement

An NHS employee will search hospital computer systems to identify all patients who had received a primary total knee replacement for osteoarthritis 2 months previously. These individuals will be sent a pre-screening notification card; 2–4 days later, they will be sent a screening study pack. Anonymised data on the age and sex of all patients sent a screening pack will be recorded. The screening pack includes a cover letter, patient information leaflet, screening questionnaire, a freepost envelope and a complimentary teabag. One reminder screening pack will be sent if no response is received within 1–2 weeks. Patients are asked to complete and return the screening questionnaire and consent form. On receipt of a completed screening questionnaire, the research team scores the OKS to identify patients with pain in their replaced knee (score of 0–14 on the OKS pain subscale).

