#### Recruitment process

Patients who score 0–14 on the screening OKS pain subscale and consent to further contact from the research team will be posted a trial information pack and then telephoned by a researcher 3–5 days later. If participating, they will then complete a second OKS via telephone with the researcher to ensure they still meet the inclusion criteria for the trial. A face-to-face recruitment consultation at the participant’s home or local hospital is then arranged. Some of the final detailed aspects of this recruitment consultation will be informed by work during the pilot phase of the trial and will follow a model consultation process [37]. If a patient would like to participate in the trial, they will be asked to provide informed, written consent. All patients will be provided with a sheet of publicly available contact details for relevant charities or organisations, such as Arthritis Care, Pain Concern and Mind. Participants are then given a baseline questionnaire to complete and return to the research team. All researchers involved in recruitment have Good Clinical Practice and trial-specific training.

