### Randomisation

After participants have provided written, informed consent and have returned a completed baseline questionnaire, they will be randomly allocated to the STAR pathway or usual care. Participants will be informed of their allocation by a member of the research team. Randomisation occurs as soon as possible after the baseline questionnaire is received. Randomisation with allocation concealment is conducted remotely via the Bristol Randomised Trials Collaboration using a web-based randomisation system. Randomisation takes place on a 2:1 basis to ensure that the intervention service is running at sufficient capacity to enable a pragmatic assessment of its clinical and cost-effectiveness. Moreover, if the intervention is operating to a sufficient degree of capacity, then per-protocol and Complier Average Causal Effect analyses will be more reliable and have higher power. To ensure reasonable balance between the two treatment groups, allocation is minimised by pain severity and pain interference scores for the replaced knee (assessed with the Brief Pain Inventory Severity and Interference Scales and categorised into tertiles based on data from a previous study [30]), and stratified by trial centre.

Blinding of participants and trial personnel to treatment allocation is not possible due to the nature of the intervention. After participants have been randomised, the research team will send the participant and their General Practitioner (GP) a letter to inform them of treatment allocation.

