### Intervention

Participants randomised to the intervention group will receive usual care and the STAR intervention, which consists of a 1-hour-long assessment clinic appointment with a trained Extended Scope Practitioner (a registered allied healthcare professional with specialist training in orthopaedics) and up to six telephone follow-up calls over 12 months (Fig. 3). Adherence to the intervention is defined as attendance at the assessment clinic appointment. Participants will be offered an assessment clinic appointment as soon as possible after randomisation, ideally within 1 week. Booking an appointment is arranged over the telephone and confirmed by letter.

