### Resource use

Resources used in relation to the intervention (including initial face-to-face assessment and telephone contacts) will be recorded on a standardised proforma. Use of health services including primary, secondary and tertiary care, use of personal social services and additional costs (private healthcare, travel, lost income, home modifications) will be collected in the follow-up questionnaires at 6 and 12 months after randomisation. Participants are provided with resource diaries and prescribed medication folders to prospectively record and document any health resources they have used to assist them in the completion of the questionnaires [53]. Resource use data, including inpatient stays and outpatient visits for all participants at the treating hospitals, will be obtained from hospital electronic systems or extracted from hospital records and recorded on a standardised proforma.

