### Cost-effectiveness analysis

The primary cost-effectiveness analysis will take an NHS and Personal Social Services perspective. A secondary analysis will take a broader perspective to include patients’ costs. Only resources used in relation to the treatment of chronic pain will be measured from randomisation to 12 months follow-up. All resources will be valued using routine data sources and information from hospital finance departments. All analyses will be on an intention-to-treat basis and there will be no discounting of costs or effects given the 1 year duration of the study. The primary outcome for the economic evaluation will be the Quality Adjusted Life Year (QALY). The difference in costs and QALYs between the arms will be assessed using the Net Benefit framework using appropriate regression models adjusted for baseline values of the minimisation/stratification variables. Additionally, the difference in costs and those in primary outcomes will be examined. If no arm is dominant, then incremental cost-effectiveness ratios will be calculated using, if appropriate, Seemingly Unrelated Regressions to account for the potential correlation between costs and the primary outcomes. Given the number of important secondary outcomes, a cost consequence analysis will also be conducted in relation to these outcomes. Uncertainty will be addressed using cost-effectiveness acceptability curves and sensitivity analyses.

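### The economic analysis leaves out the cost of screening, which the protocol names as part of the STAR pathway, so the cost of adopting the pathway is understated, although the randomised comparison itself is not biased

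*Protocol article*

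**What the plan says.** All references are to the protocol article.

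- **Background.** The pathway is one "which consists of early postoperative screening to identify patients with pain and an assessment clinic at 3 months postoperatively", followed by telephone follow-up as needed. The same paragraph closes with the trial's aim, the clinical and cost-effectiveness of the care pathway. The Aim section repeats the economic objective for the care pathway.
- **Intervention.** Participants in the intervention arm get usual care plus "the STAR intervention, which consists of a 1-hour-long assessment clinic appointment with a trained Extended Scope Practitioner", and up to six calls. Screening is not mentioned. The Abstract and item 13 of the registration table (Appendix, Table 1) give the same two components.
- **Screening process.** Hospital records are searched to "identify all patients who had received a primary total knee replacement for osteoarthritis 2 months previously". These patients get a card, a questionnaire pack and, if needed, one reminder.
- **Recruitment process.** Those who score 0–14, agree to contact and wish to take part are telephoned, and "they will then complete a second OKS via telephone with the researcher to ensure they still meet the inclusion criteria for the trial".
- **Randomisation.** "After participants have provided written, informed consent and have returned a completed baseline questionnaire, they will be randomly allocated".
- **Resource use.** "Resources used in relation to the intervention (including initial face-to-face assessment and telephone contacts) will be recorded on a standardised proforma".
- **Cost-effectiveness analysis.** "Only resources used in relation to the treatment of chronic pain will be measured from randomisation to 12 months follow-up".
- **Usual care.** A 6-week follow-up at every site, an extra 3-month appointment at one, and a surgeon's review on request. No pain screening step is described.

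**The concern.** The protocol uses two definitions of what is being evaluated. One starts with screening and the other starts with the clinic. The economic section does not say which of them it values, but its costing rule settles the matter in effect. Screening is not treatment, and it happens before randomisation, so it fails both parts of the rule.

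This matters because the Discussion offers the results to commissioners and suggests that the intervention could improve early identification as well as management. A service that adopts the pathway must first find its patients, and usual care as described has no step that does so. Finding them is therefore an added cost of adoption, multiplied by the number of patients screened per patient found. As planned, that cost enters the net benefit, any incremental cost-effectiveness ratio (ICER) and the acceptability curves as zero.

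**Working it through.** The document gives no cost, ICER or net-benefit figure, so there is no stated result to reproduce. The sample size is not affected.

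**Step 1: which cost is left out, and for which question**

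| Question | Is screening part of it? | Effect of the costing rule |
|---|---|---|
| Clinic plus calls against usual care, in patients already screened (Abstract, Intervention, Table 1 item 13) | No. Both arms had it before randomisation | Screening cancels; no bias in incremental cost |
| Pathway as the Background defines it, against usual care as a service provides it | Yes, on the pathway side only | Incremental cost understated by the cost of finding one eligible patient |

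**Step 2: size of the omitted cost**

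Cost omitted per patient identified = c / (p × r), where
- p is the proportion of responders scoring 0–14. The protocol's figure of about 20% (Background, Discussion) is the prevalence of chronic pain, not the yield of this questionnaire at 2 months. It is used here as a stand-in, with 10% and 15% as assumed alternatives.
- r is the response rate to the screening pack. It is not in the document and is assumed to be 50% to 100%.
- c is the cost per patient sent a pack. It is not in the document and is assumed to be £2 to £10.

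At p = 20% and r = 100%: 1 / (0.20 × 1.00) = 5 patients screened per patient identified. Any non-response raises this number.

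| p | r | Packs per patient identified, 1/(p × r) | Cost at £2 to £10 per pack |
|---|---|---|---|
| 20% | 100% | 5.0 | £10–£50 |
| 20% | 75% | 6.7 | £13–£67 |
| 20% | 50% | 10.0 | £20–£100 |
| 15% | 100% | 6.7 | £13–£67 |
| 15% | 75% | 8.9 | £18–£89 |
| 15% | 50% | 13.3 | £27–£133 |
| 10% | 100% | 10.0 | £20–£100 |
| 10% | 75% | 13.3 | £27–£133 |
| 10% | 50% | 20.0 | £40–£200 |

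The full range is £10 to £200 per patient identified.

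**Step 3: the same amount on the net-benefit scale**

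At an assumed £20,000 per QALY, £10 / £20,000 = 0.0005 QALY and £200 / £20,000 = 0.010 QALY.

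**Step 4: the effect side**

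Controls are also screened, telephoned and given a sheet of support organisations, and their GP is sent a letter. Any benefit from these steps is removed from the difference between arms. Adding screening cost therefore corrects the cost side only. The trial cannot estimate what screening itself does to pain or QALYs.

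**The case against.** The strongest reply is that every operational definition of the randomised intervention is clinic plus calls, and that the Discussion frames the comparison as one in patients already screened. For that question a step common to both arms cancels, and nothing is biased. This stands. A reader might infer that the trial's own incremental cost is biased downwards or its cost-effectiveness overstated. The document does not support that, because the randomised contrast is internally sound and any effect of screening on controls is also removed from it.

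Three further points stand in whole or in part.
- Charging screening to one arm in the base case would set a cost against an effect contrast that excludes screening. It belongs in a scenario analysis.
- Trial screening is not service screening. The information leaflet, the teabag and possibly the pre-notification card and researcher's call serve research ends, so costing them all could overstate what a service would pay.
- The size rests mostly on assumptions.

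Two replies do not stand. The list of intervention resources in the Resource use section is introduced by a word that leaves it open, but this does not undo a window that begins at randomisation. Nor is this merely detail left to a fuller economic plan: the exclusion is a stated restriction, and a later plan that costed screening would contradict it.

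**Conclusion.** The concern holds for the pathway as the Background defines it. The incremental cost of adopting that pathway is understated by the cost of identifying each eligible patient. That the omitted cost is above zero follows from the document, since screening takes resources and usual care as described does not include it. The factor of at least 5 patients screened per patient found holds if the protocol's 20% is the yield. The monetary range of roughly £10 to £200 depends on assumed yield, response and unit cost. It may be modest, and the document does not show that it would change a decision.

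The comparison of clinic plus calls in already screened patients is not biased. Whether the full pathway is more or less cost-effective than the trial will report cannot be settled, because the effect of screening is unknown and lies outside the contrast.

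**What to change.** 1. Keep the randomised comparison, costed from randomisation, as the base case.
2. Add to the Cost-effectiveness analysis section a pre-specified scenario that charges each intervention participant the service-relevant cost of identifying one eligible patient: mailing, reminder and scoring, plus the repeat OKS if a service would use it, divided by the number scoring 0–14. Leave out research-only items such as consent materials.
3. Report net benefit, the ICER where one is calculated, and acceptability curves with and without this cost. Note that the scenario changes costs only.
4. State that the clinical and base-case economic conclusions apply to the assessment clinic and telephone follow-up in patients already identified by screening.

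The counts should be at hand, since the trial logs everyone sent a pack and scores every returned questionnaire. The price is a small costing exercise and a slightly less favourable cost figure in the scenario. Trial conduct and sample size do not change.

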## Methods/Design

This protocol follows guidance from SPIRIT (Standard Protocol Items: Recommendations for Interventional Trials) [33, 34]. A SPIRIT figure for the schedule of enrolment, interventions and assessment is provided in Fig. 1 and a SPIRIT checklist is provided in Additional file 1.

**Fig. 1 Fig1:**
[figure not shown]
SPIRIT Figure for the schedule of enrolment, interventions and assessments

### Aim

The primary aim of this trial is to evaluate the clinical effectiveness of a new care pathway (‘the STAR pathway’) when compared with usual care for people with chronic pain after knee replacement. Secondary objectives of embedded aspects of the trial include:

1. Pilot phase with qualitative work to optimise recruitment and refine trial processes;

2. Economic analysis to evaluate the cost-effectiveness of the care pathway;

3. Qualitative study with patients who received the intervention to explore their experiences of the care pathway.

### Design

Core trial information are presented in Appendix – WHO Trial Registration Data Set. This is a pragmatic, parallel, two-arm, superiority, multi-centred randomised controlled trial using 2:1 intervention:control randomisation, with an internal pilot phase and embedded economic evaluation and qualitative studies. The trial is currently taking place at four high-volume National Health Services (NHS) centres for total knee replacement, and will be expanded to include 8–10 trial sites.

